### Data collection

Potentially eligible subjects, who have signed the consent form to participate in this trial, will fill out a form for collecting sociodemographic and anthropometric information, such as weight and height, and headache characteristics, such as pain intensity and disease time (in years). All patients will receive a headache diary, which should be filled out daily for 30 days, thus providing baseline data for the frequency and intensity of migraine attacks.

After 30 days, volunteers will return for the initial assessment, which includes questionnaires and physical examination, as described in Fig. 1. After the first assessment, the participants will be randomized. Throughout treatment, the headache diary must be filled out monthly to assess the frequency and intensity of attacks. Participants will be reevaluated at the end of the fourth, eighth, and twelfth weeks of treatment. These assessments will follow the same protocol as the initial assessment, including the Patient Global Impression of Change Scale [35]. All primary and secondary outcomes will be evaluated at the fourth, eighth, and twelfth weeks of the treatment period. Follow-up will then occur at 1, 2, and 4 months after the end of the treatment period to assess headache-related disability, in addition to frequency (days/month) and intensity of headache, using data from the headache diary.

**Fig. 1 Fig1:**
[figure not shown]
Study schedule summary. Legend: *HIT-6* Headache Impact Test; *NDI* Neck Disability Index; *ASC-12* 12 item Allodynia Symptom Checklist; *TSK* Tampa Scale for Kinesiophobia; *PCS* Pain Catastrophizing Scale; *EQ-5D-5L* 5-level EQ-5D tool for measuring the quality of life; *PGIC* Patient Global Impression of Change Scale; *CROM* Cervical Range of Motion; *PPT* Pressure Pain Threshold; *FRT* Flexion Rotation Test; *CCFT* Craniocervical Flexion Test.

Treatment time (12 weeks)

### Questionnaires

*Headache Impact Test* (HIT-6) is a tool assessing the headache impact with good psychometric properties among patients with headache [36]. The final score varies between 36 and 78 and is classified as little or no impact (≤ 49 points), some impact (50–55 points), considerable impact (56–59 points), and severe impact (≥ 60 points) [37]. For headache disability, good results will be attributed to those individuals with a reduction ≥ 6 points, which is the MCID for this scale [34].*Neck Disability Index* (NDI) is a questionnaire assessing neck pain-related limitations in daily living activities such as personal care, sleep, and reading. The score ranges from 0 to 50 points, and the individual can be classified as: without disability (0–4 points), mild disability (5–14 points), moderate disability (15–24 points), severe disability (25–35 points), and total disability (> 36points) [38, 39]. This tool is valid and reliable, with good responsiveness [40, 41].*12 item Allodynia Symptom Checklist* (ASC-12) [42] is a 12-item questionnaire to identify the presence of and classify the severity of cutaneous allodynia based on discomfort or pain felt during migraine crisis to perform activities of daily living, such as combing the hair or wearing glasses. The score can be up to 24 points and is classified as: no allodynia (0–2 points), mild allodynia (3–5 points), moderate allodynia (6–8 points), or severe allodynia (≥ 9 points). Florencio et al. (2012) translated and validated the Brazilian version of this tool, which is evidenced as quick, practical, and reliable for the evaluation of cutaneous allodynia [43].*The Tampa Scale for Kinesiophobia* (TSK) is a 17-item scale originally developed to measure the fear of movement, with a total score between 17 and 68 points [44]. This questionnaire has good reliability and psychometric applicability for the cervical region, and a correlation with depression and catastrophic symptoms [45].*Pain Catastrophizing Scale* (PCS) [46] is a 13-item questionnaire that measures pain-related catastrophizing and consists of three subscales: assessing helplessness, magnification, and rumination. The total score is calculated as the sum of all items, ranging from 0 to 52 points [47]. It has been demonstrated to be a reliable and valid measure of catastrophizing [46].EQ-5D-5L [48] is a version of the 5-level EQ-5D tool used to assess health-related quality of life [49]. This version comprises five dimensions: mobility, self-care, usual activities, pain/discomfort, and anxiety/depression. The version also includes the visual analog scale of the EQ (EQ-VAS), which records the patient’s self-assessment of health from “the best health you can imagine” to “the worst health you can imagine.”*The Patient Global Impression of Change Scale* (PGIC) is used to quantify individuals’ perception of worsening or improvement. The PGIC is a scale of seven items in which individuals rate their improvement in association with an intervention. The patients’ classification is present from 1 (no change or worsening) to 7 (a great deal better) [35].

### Pressure pain thresholds

The pressure pain threshold (PPT) will be assessed using a digital manual dynamometer (DDK-20 Kratos®) adapted for algometry, with participants in the sitting position. The PPT is a measure that has good reliability in healthy adults in the cervical region [50]. The trained examiner will apply a constant pressure of 1.0 kg/cm^2^/s with the device optimally positioned perpendicular to the anatomical surfaces to be evaluated. A digital metronome with a frequency of 1 Hz will be used in all evaluations to provide audio feedback and to standardize the speed of pressure application. Participants will be asked to signal as soon as they first feel pain. Pressure pain thresholds will be assessed randomly, and bilaterally over the upper trapezius, temporal, sternocleidomastoid, suboccipital, anterior scalene, and levator scapulae muscles, three times.

### Cervical range of motion

Cervical range of motion and cervical muscle strength will be evaluated using the Multi-Cervical Unit equipment (MCU, BTE Technologies, Inc., 2006). This tool has excellent reliability for all movements (ICC, 0.82 to 0.96) [51]. Two trials will be collected for each movement (flexion, extension, lateral flexion, and rotation) to determine the cervical range of motion with the volunteer in a sitting position. The head brace will be positioned comfortably around the volunteer’s head.

### Cervical muscle strength

To measure cervical muscle strength with the MCU, a load cell will be plugged into the brace that was used to measure the isometric force applied during cervical flexion, extension, and lateral flexion movements. There will be familiarization with the test by submaximal contraction of flexion and extension before the beginning of data collection. The evaluator will then request maximal isometric voluntary contractions through three repetitions of 3 s for each of the muscle groups. There will be a 20-s interval between each repetition and a 3-min interval between each movement to avoid muscle fatigue. The strength assessment of this equipment presents excellent reliability for all movements (ICC, 0.923–0.99) [51].

### Flexion rotation test (FRT)

Restricted movements of the upper cervical spine (C1-C2 segment) will be evaluated by the flexion rotation test (FRT) using the Cervical Range of Motion (CROM®) device over to the patient’s head. Participants will be positioned in the supine position with the head supported by the examiner’s hand, which will perform maximum passive flexion of the cervical spine followed by the maximum passive cervical rotation on each side [52–54]. The final range of motion is determined when the examiner perceives resistance or when the patient reports pain in the upper cervical segment. The FRT was considered positive when the subjects had a range of motion of less than 34° for right or left rotation [53, 54].

### Craniocervical flexion test (CCFT)

The craniocervical flexion test (CCFT) is a neuromuscular low-load test used to assess deep cervical flexor activation and endurance [55]. The test will be performed with the individual in a supine position, with a pressure biofeedback unit (Stabilizer Chattanooga South Pacific; USA) placed behind the neck and inflated up to 20 mmHg. Individuals will be instructed to perform a slow and gentle head-nodding action (craniocervical flexion) over five incremental stages (2 mmHg at each stage). Each stage will be maintained for 10 s. The participants will perform two 2-s repetitions at each stage to become familiar with the task. They will perform the CCFT by holding the target level for 10 s with a rest period of 30 s between levels without any compensation. The test will be interrupted when any compensation is identified, such as simultaneous palpable contraction of superficial flexors, and the latest stage performed without any compensation will be registered as the targeted stage [55].

### Statistical methods

A descriptive analysis of all variables will be performed, and the data will be reported as mean, standard deviation, and 95% confidence intervals. The statistical analysis will be performed according to the nature and distribution of each variable and be evaluated to verify any changes in the parameters and differences between the groups after the end of the protocol. For the analysis of outcomes, a significance level of 0.05 will be considered.

The intention-to-treat analysis will include all randomized volunteers, regardless of their treatment adherence in the evaluations and analyses [56]. The between-groups comparison will be performed using a mixed-effect regression model for all outcomes, considering the group effect, time effect, and group vs. time interaction. In addition, in those outcomes without predetermined MCID values, it will be calculated based on a distribution-based approach. The clinical relevance of the differences between groups will be classified according to the combination of MCID and effect size (ES), as suggested by Armijo-Olivo et al. [57]. The ES will be estimated by using Cohen’s d. The clinically relevant difference should present a mean difference that is more significant than MCID and ES > 0.4.

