### Outcomes

#### Primary

The primary outcome will be headache impact, measured using the Headache Impact Test (HIT-6), requiring a decrease of at least 6 points in the headache-related impact measured by the HIT-6 [34], which will be applied at the baseline, and at four, eight, and 12 weeks of treatment, and at follow-ups at 1, 2, and 4 months.

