### Sample size

The sample size was calculated for the primary outcome, the HIT-6. It was based on a mean reduction of six points and a standard deviation of 6.03, while adopting a significance level (α) of 0.05 and power of 90%. We estimated 21 individuals per group, and considering a 15% loss to follow-up, 25 individuals per group will be required. Therefore, 75 individuals will be included in this clinical trial. An effect size of ≥ 6 points at HIT-6 is the minimum clinically important difference (MCID) for this scale [34]. The standard deviation was derived from a sample of nine volunteers from our database of previous studies.

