### Limitations

It should be recognized that this protocol has some limitations. First, patients will be recruited from both tertiary headache centers and the general population. The sample may be composed of cases with distinct severities of migraine. Therefore, there must be a minimum of 3 days of headache per month, and those with concomitant headache diagnoses should be excluded. In addition, due to the greater female preponderance observed in migraine [68], we may have more women than men included in this study. As we will not control for gender distribution among the groups, we cannot guarantee the ability to demonstrate gender differences in the response to treatment. Moreover, the allocation sequence generation and concealment used should guarantee an appropriate randomization process, which avoids the influence of either known or unknown prognostic factors [69].

Second, it will not be possible to blind the participants and the therapist who will apply the interventions, considering the proposed treatment approach. This would increase the risk of bias due to deviation from the intended intervention, affecting mainly the participant’s adherence [69]. According to the Cochrane risk of bias assessment [69], if participants are aware of their assigned intervention, it is more likely that health-related behaviors will differ between the intervention groups. However, the planned interventions of this protocol itself expect different behaviors from the participants (active or passive behaviors). The co-intervention using the prescribed medication is also expected and controlled in the current study by the use of a headache diary. Patients who start a new medical treatment during the trial screening and selection will be recruited to start the study protocol only after 3 months, which is the time required to stabilize the medication’s effects. The patients will be instructed to use only the prescribed medications when appropriate, but the use of non-prescribed medications should also be mentioned separately in the pain diary.

Finally, the results of this trial will be restricted to the immediate effects on most of our variables and mid-term effects on clinical outcomes (headache impact, frequency, and intensity). This was a methodological choice to avoid a higher proportion of dropouts in this trial. However, we prioritized patient-reported outcomes related to migraine.

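### The stated mixed model names no baseline covariate or common baseline mean, so it gives up precision that the pre-randomisation measurements could supply (an efficiency point, not bias)

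*Protocol article*

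**What the plan says.** Statistical methods in the protocol article fixes the main analysis in one sentence: "The between-groups comparison will be performed using a mixed-effect regression model for all outcomes", "considering the group effect, time effect, and group vs. time interaction". No baseline covariate is named there or elsewhere, and nothing says that the groups share a baseline mean. The section also does not say whether baseline is one of the levels of time.

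Baseline values will be available. The Primary outcome section describes HIT-6 as a questionnaire "which will be applied at the baseline, and at four, eight, and 12 weeks of treatment, and at follow-ups at 1, 2, and 4 months". Under Data collection, a 30-day diary and the initial assessment (questionnaires and physical examination) come first, and then: "After the first assessment, the participants will be randomized". The exception is the PGIC, which rates change and is added only at the re-evaluations.

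The Sample size section gives the planning values: "It was based on a mean reduction of six points and a standard deviation of 6.03", with α 0.05, power 90%, 21 per group, and 25 after 15% loss. It does not say whether 6.03 is the SD of change or of a single score.

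**The concern.** A group-by-time model can use baseline in two ordinary ways, and neither is the most precise. With baseline as a time level and a free mean in each group, the week-12-versus-baseline interaction is a difference of change scores. With baseline omitted, the contrast is a difference of post-treatment scores. Randomisation makes the expected baseline means equal across groups, and the stated model makes no use of that.

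The loss is worth avoiding in a trial of this size. There are 25 per arm, and the Limitations section expects varied patients: "The sample may be composed of cases with distinct severities of migraine". The same section relies on sequence generation and concealment for a process "which avoids the influence of either known or unknown prognostic factors". Randomisation gives that balance only in expectation; conditioning on the measured baseline deals with the part left to chance. What is at stake is the width of the confidence intervals and the power of the group contrasts.

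**Working it through.** **Inputs.** From the Sample size section: difference 6, SD 6.03, α 0.05 (taken as two-sided), power 90%, 21 evaluable and 25 randomised per group. Assumed, because the protocol gives none: a baseline-to-follow-up correlation r of 0.3, 0.5 or 0.7, and equal variances at baseline and follow-up.

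**The plan's own figure.** Two-sample normal formula: n = 2 × (1.960 + 1.282)² × 6.03² / 6² = 21.2. Rounded up this is 22, against the stated 21. Power at 21 per group is 0.897 (normal) or 0.882 (noncentral t, 40 degrees of freedom). Allowing for 15% loss, 21 / 0.85 = 24.7, so 25 per group and 75 in all. The stated size is therefore reproduced to within one patient per group, and it assumes no baseline adjustment.

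**Relative variances.** With σ² the variance of a single score, the variance of the group contrast is proportional to:
- post score: σ²
- change score: 2(1 − r)σ²
- baseline-adjusted: (1 − r²)σ²

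Hence adjusted/change = (1 + r)/2 and adjusted/post = 1 − r².

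| r | adjusted/change | reduction | adjusted/post | reduction |
|---|---|---|---|---|
| 0.3 | 0.65 | 35% | 0.91 | 9% |
| 0.5 | 0.75 | 25% | 0.75 | 25% |
| 0.7 | 0.85 | 15% | 0.51 | 49% |

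**Check in the longitudinal model.** Generalised least squares with three groups, 21 per group, four visits (baseline, weeks 4, 8 and 12), compound symmetry and single-score SD 6.03 gives these standard errors for the week-12 contrast:

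| r | free baseline means | common baseline mean |
|---|---|---|
| 0.3 | 2.20 | 1.78 |
| 0.5 | 1.86 | 1.61 |
| 0.7 | 1.44 | 1.33 |

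The first column equals the change-score formula, 6.03 × √(2(1 − r) × 2/21). The second equals the covariance-adjusted formula, 6.03 × √((1 − r²) × 2/21). The squared ratios are 0.65, 0.75 and 0.85, as in the table above.

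**Power at 21 per arm, difference 6, one contrast** (noncentral t, two-sided 0.05).

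If 6.03 is the SD of change, the adjusted SD is 6.03 × √((1 + r)/2) = 4.86, 5.22 and 5.56 for r = 0.3, 0.5 and 0.7. Power goes from 88% unadjusted (the same for every r) to 97%, 95% and 93%.

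If 6.03 is a single-score SD:

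| r | SD of change | power, change | power, post | adjusted SD | power, adjusted |
|---|---|---|---|---|---|
| 0.3 | 7.13 | 76% | 88% | 5.75 | 91% |
| 0.5 | 6.03 | 88% | 88% | 5.22 | 95% |
| 0.7 | 4.67 | 98% | 88% | 4.31 | 99% |

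**The case against.** The strongest reply is that a journal article condenses the model to one sentence. It lists the terms considered and does not say that there are no others, so a fuller specification may sit in an analysis plan that is not shown. That limits the point: the article makes no error and does not contradict itself. The point still stands as an improvement, because the published list of terms is specific and a plan that used baseline more fully would be adding to it.

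Three stronger readings are tempting, and the document does not support them.

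- A reader might infer that the analysis ignores baseline altogether. HIT-6 is scheduled at baseline and six later times, and the usual reading of group by time in such a design makes baseline a time level. The interaction then subtracts baseline. It uses baseline, though not in the most precise way.
- A reader might infer that chance imbalance at baseline invalidates the comparison. Both unadjusted contrasts are valid under randomisation, and the change-score contrast already removes the observed baseline difference (over-correcting for it when r is below 1 and variances are equal).
- A reader might infer that the trial is underpowered. The 76% figure needs a single-score SD, baseline as a time level and a correlation of 0.3, all together. The Sample size section pairs 6.03 with a mean reduction, so the SD of change is at least as natural a reading. On that reading, unadjusted power is 88% whatever the correlation.

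Two possible extensions should also be left out. The protocol does not name recruitment source among the recorded variables, so it is not proposed as a covariate. Nothing here shows how far adjustment would offset the cost of making two comparisons.

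**Conclusion.** This is a free improvement in efficiency; it corrects neither a bias nor an invalid test. For any correlation strictly between 0 and 1 (equal variances), conditioning on baseline is more precise than either contrast the stated model can give. How large the gain is depends on the correlation, on which SD 6.03 represents and on whether baseline is a time level, none of which the protocol states. Across r from 0.3 to 0.7 the variance falls by 15% to 35% against change scores, or by 9% to 49% against post scores. The gain in power ranges from about 1 percentage point (98% to 99%: single-score SD, change contrast, r = 0.7) to about 15 (76% to 91%: same reading, r = 0.3). In every case shown, adjusted power exceeds the planned 90%.

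**What to change.** Add one sentence to Statistical methods, before data are seen, stating how baseline enters the mixed model. Either of these serves:

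1. Treat baseline as one of the responses and constrain the three group means to be equal at baseline (constrained longitudinal analysis). This sits well with the plan to include all randomised participants.
2. Model the post-randomisation visits, with the baseline value and its interaction with visit as covariates.

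In both, report the group contrasts at each visit. Analyse the PGIC without a baseline term, since it has no pre-randomisation value. State in the Sample size section whether 6.03 is the SD of change or of a single score, so that the gain can be judged. The cost is the drafting alone: no extra participants, visits or measurements.

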## Discussion

### Potential impact and significance of the study

The multimodal approach proposed in this clinical trial has been discussed to treat different dysfunctions of the neck [58], mainly because of its relationship with the cervical spine and the inclusion of education in patients with chronic disease [19]. However, there are no previous studies that used a multimodal physical therapy treatment for migraine, or evidence of this multimodal protocol’s effects compared to manual therapy techniques or therapeutic pain neuroscience education alone, separately. Due to the presence of cervical dysfunctions and musculoskeletal disorders [25, 59–61], and their psychosocial factors, there are reasons to infer that these individuals with migraine will benefit from this multimodal approach.

Regarding the treatments already described, Bevilaqua-Grossi et al. proposed adding a combination of manual therapy with trigger point release and cervical stretching to the pharmacological treatment, and observed clinical improvement in the frequency and intensity of migraine attacks when associated with the variables of global perception of change and satisfaction with treatment, as well as a significant increase in the pressure pain threshold when compared to the control group [9]. Despite the positive results, no other aspects of cervical dysfunctions that have already established in individuals with migraine, such as decreased cervical muscle strength [23], cervical disability [62–64], and the inclusion of therapeutic pain neuroscience education for the treatment of these patients were considered in this previous trial.

Migraine is accompanied by different musculoskeletal and functional dysfunctions of the cervical spine [25, 59–61], suggesting that patients will benefit from a multimodal treatment potentially including relaxation techniques, manual therapy that includes myofascial release, trigger point release, cervical mobilizations and stretching, and exercise programs of the cervical spine muscles, along with therapeutic pain neuroscience education in the same treatment protocol.

There is also little evidence regarding the self-management of migraines with home orientation [65]. We know that a program of therapeutic pain education on the disease, its pharmacological, nutritional, and exercise orientation, and stretching was effective in reducing the frequency of headache by 50% in 34% of patients, in addition to improvements in disability, quality of life, self-efficacy, and satisfaction with treatment [66]. Thus, a 50% reduction in the frequency of pain was observed when patients underwent self-administered message-based behavioral interventions [67]. However, little is currently known about the effectiveness of a self-approach to migraine management, including physiotherapeutic orientation, and how much this approach could contribute to patient improvement. If these approaches are more effective together than separately, then consequently, we hope to find a greater reduction in headache-related disability, one of the most addressed issues in the literature due to the high disability rate present in the migraine population [68]. The results will be informed to participants, healthcare professionals, the public, and other groups through articles published in journals of major impact, social media of our search group, lectures for the community, and national and international events.

